# A medical peer-delivered intervention comprising brief motivational interviewing via instant-messaging interaction to reduce drug misuse among youth in Hong Kong: A protocol for a randomised controlled trial

**DOI:** 10.1186/s13722-021-00241-x

**Published:** 2021-05-22

## Abstract

**Aims:**

Youth are frequently exposed to drugs, and most youth who misuse drugs are reluctant to seek help from services due to the worry of others being judgmental, lacking expertise, exposing their personal information, or informing their parents. Considering these concerns, we propose to evaluate the effectiveness of a medical peer-delivered intervention comprising brief motivational interviewing via instant-messaging interaction in reducing drug misuse among youth in Hong Kong.

**Methods:**

A two-group single-blind, randomised controlled trial will be conducted. Multiple approaches, including online and face-to-face methods, will be used to recruit the participants. The participants, aged 25 years or younger and reporting any drugs that they have taken within the past 30 days, will be recruited and randomised to receive either brief motivational interviewing via interactive instant-messaging (the intervention) or general health text-messages (comparator). The primary outcome will be the change in the participants’ reductions in self-reported drug consumption at 12 months compared to that at baseline. The secondary outcomes will be the changes in the drug-abusing participants’ reductions in self-reported drug consumption at 6 months, the changes in the drug-quitting participants’ 6- and 12-month contemplation stages and relapse risk compared to that at baseline, 30 days’ self-reported drug abstinence at 6 and 12 months, and the treatment needs and motivation at 6 and 12 months compared to that at baseline. The effectiveness of the proposed intervention will be examined with adjusted regression models, with adjustment for baseline characteristics and the use of an intention-to‐treat approach.

**Discussion:**

This proposed study will be the first randomised controlled trial to assess the effectiveness of a medical peer-delivered interactive intervention to reduce drug misuse among youth in Hong Kong. The proposed intervention has the potential to increase the help-seeking behaviour and intention to quit among youth who misuse drugs. As a result, more youth misusing drugs may be helped to abstain from drugs. This proposed study will inform decisions on whether it is worthwhile to invest resources in large-scale implementation of such an intervention.

## Introduction

Drug misuse is a worldwide problem, especially among youth. In Hong Kong, there is easy access to a wide range of illicit drugs from multiple sources, which has led to an increase in drug misuse among youth. According to the Central Registry of Drug Abuse Report in Hong Kong, 87.3 % of people with a drug use disorder reported that they first used drugs at 25 years of age or younger [1]. Statistics from the Central Registry of Drug Abuse show that the number of students who claimed to have used drugs increased by 23 % between 2014/15 and 2017/18 and that 81 % of those had begun using drugs before 15 years of age [1, 2]. In addition, official figures revealed that 58 % of students who misuse drugs only at their own home or a friend’s home, which was a substantial increase from the 43 % recorded in 2008 [2]. These statistics show the alarming amount and nature of drug misuse and hidden drug-taking among youth in Hong Kong.

An early age at first drug use is strongly associated with the risk of developing a substance-use disorder later in life [3]. Youth who persistently misuse substances often have an array of problems, such as academic difficulties, physical and/or mental health-related problems, poor peer relationships, a tendency to exhibit risky sexual behaviour, an increased incidence of blood-borne diseases, and involvement with the juvenile justice system [3–5]. In addition, there are harmful consequences for family members of those who misuse drugs and for their communities and wider society [6]. As a result, youth drug misuse in Hong Kong has become a major problem that cannot be overlooked.

A combination of medical treatment and counselling is the most common treatment for people with drug misuse [7]. However, of the drug-misusing youth surveyed, more than half reported that they had never attempted to abstain from using drugs, only 12.2 % had attempted to seek help, and more than 75 % reported they would not accept medical treatment because they did not believe that they were addicted [2]. Many non-pharmaceutical interventions have previously been applied, but a meta-analysis found that these interventions were ineffective at helping youth stop misusing drugs [7, 8]. A primary reason for this failure was that the patient education methods used may have made drug-misusing youth resistant to accepting interventions [8]. Previous studies have confirmed that recovery from drug misuse is influenced by users’ intentions to change, which are directly determined by their perceptions of anti-drug education and their perceived self-efficacy to change [3]. However, their attitudes, social influences, and demographic characteristics have more indirect effects on recovery from drug misuse [9]. Another reason for the failure of non-pharmaceutical interventions may be that standard interventional content may fail to meet the personal needs of people who misuse drugs. In addition, the meta-analysis also showed that individual interventions comprising more than one session had a stronger effect, whereas brief interventions provided an insufficient number of sessions to support behaviour changes among youth who misuse drugs [8]. Furthermore, qualitative interviews with youth drug misusers have shown that adolescents were reluctant to seek help from sources who they believed would be judgmental, lacked expertise, would reveal their personal information to others, or would inform their parents [10]. These findings demonstrate that feasible, individualised, and effective non-pharmaceutical interventions must be developed to assist Hong Kong’s drug-misusing youth to change their unhealthy behaviour.

### Conceptual framework

Our proposed intervention will be developed with the use and guidance of (1) medical peer-delivered counselling, (2) instant messaging, and (3) brief motivational interviewing.

#### Medical peer-delivered counselling

The use of peer counsellors rather than general counsellors increases the appeal of addiction services to youth and young adult drug users [11]. Because most young people are not eligible to hold positions of power in society, they are subject to authority. This power differential means that communication between adults and youth can be difficult, which manifests as a knowledge gap when attempts are made to engage youth in drug-misuse reduction initiatives. In contrast, the equality in power status between youths means that peer-delivered risk communication is more likely to be successful [11]. In addition, the psychological and social factors associated with the initiation and continuation of drug misuse differ between young people and older adults. Worries about the stigma of drug use, being judged, the exposure of personal information, their parents being informed, not knowing what to expect from the treatment, and major lifestyle changes are the main barriers that prevent youth and young adults from seeking substance use treatment [10, 12]. Youth who misuse substances often experience an array of problems, including academic difficulties, health-related problems (including mental health problems), poor peer relationships, and risky sexual behaviour. Due to their similar age, peers can address the concerns of youths by drawing on their own experiences [13]. Knowledge-sharing and empathetic listening from peers may be more effective at helping drug-misusing youth to overcome or reduce their fear of the unknown regarding the treatment programme [14]. However, addiction counselling on substance use is more complex than counselling for smoking cessation or alcohol and requires more professionalism. Peers with a medical background can therefore best address youths’ concerns, as they have the combined advantages of a similar age and a better ability to master related knowledge and counselling skills than non-medical peers.

#### Instant messaging

Given the ubiquity of mobile technology among youth and the considerable logistical barriers to face-to-face-based care, instant messaging (IM) via mobile applications (apps) such as WhatsApp or WeChat is increasingly being used as a new strategy for health promotion and for enhancement of treatment compliance [13]. A previous study reported that drug-abusing clients preferred to use online counselling because it provided a private and emotionally safe environment that was less confrontational than traditional forms of counselling [15]. Therefore, interaction via smartphone apps encourages those who are reluctant to seek face-to-face help to obtain direct anti-drug misuse advice. IM also enables rapid, real-time interactions, thus delivering continual professional advice and personalised support to help drug misusers overcome drug-withdrawal symptoms.

#### Brief motivational interviewing

Motivational interviewing (MI) was originally developed in the field of alcohol misuse and has been successfully used to treat other health-related behaviours [14, 16]. In contrast to most patient education methods, MI is a direct, client-centred counselling strategy that encourages clients to explore and resolve their ambivalence and promotes their confidence in their ability to change their behaviour. Brief MI has the advantage of saving manpower and, like MI, treats individuals as advocates to initiate and continue their own behavioural change. However, individuals may experience fluctuating motivations before changing their behaviour and thus may do so in a state of ambivalence [17]. Brief MI therefore emphasises the use of shorter and simpler strategies, which include an opening strategy, asking a subject to describe a typical day, exploring the good things and the less good things about exhibiting the targeted behaviour, providing information, comparing the future and the present, exploring concerns, and helping with decision-making. Brief MI uses these strategies as part of a dynamic and interactive process to explore and resolve individuals’ ambivalence and to develop discrepancies between individuals’ core beliefs and the behaviour of not engaging in a desirable health-related lifestyle practice. This process enhances the confidence of individuals and their motivation to change their behaviour.

#### Incorporating medical peer counselling, IM, and brief MI into the promotion of drug misuse reduction among youth

A medical peer-delivered intervention via IM interaction may be more effective in helping to eliminate or reduce drug-abusing youths’ fear of personal-information exposure, in increasing their knowledge of what to expect from treatment and their ability to change their entire lifestyle, and in reducing their worries about withdrawal symptoms. This type of intervention therefore has the potential to increase help-seeking behaviour and the intention to quit among youth who misuse drugs, who are typically reluctant to seek help from services that require real-name registration. Brief MI strategies may be used to guide youth who misuse drugs to attempt a step-by-step process of behaviour change, which may enable them, with assistance, to abstain from drugs.

As stated above, the proposed intervention may be feasible and effective in reducing drug misuse among youth. However, our literature search revealed a paucity of studies that explored the effectiveness of such interventions. This proposed study will therefore involve a randomised controlled trial to determine the effectiveness of a medical peer-delivered intervention that comprises brief MI via IM in reducing drug misuse among youth in Hong Kong.

## Methods

### Study design

This proposed study will be a two-arm, parallel-group, pragmatic randomised controlled trial (RCT) with a 1:1 allocation ratio. It will compare the reduction in drug misuse at 12 months in two groups of youths: those who are individually randomised to participate in the intervention group, who will receive medical peer-delivered, interactive brief MI via IM; and those in the control group, who will receive general health information via text messaging (Fig. 1).

**Fig. 1 Fig1:**
[figure not shown]
CONSROT Flow diagram

### Resource and setting

This proposed study will be conducted in association with the Medical Peer Addiction Counselling Quitline Service (MedPAC Quitline), supported by the Beat Drugs Fund, Narcotics Division, Security Bureau of Hong Kong. The team of the School of Nursing at the University of Hong Kong established this first peer-oriented drug misuse quitline in 2020. Trained youth and young adult counsellors with a medical background provide peer-oriented drug-misuse counselling via MedPAC Quitline to drug-abusing youth and young adults and actively refer those in need to further treatment and rehabilitation services.

### Participants and sampling

Callers to the MedPAC Quitline and those who are actively recruited from schools and communities will be eligible service targets for the MedPAC Quitline. Youth who misuse drugs and have contacted the MedPAC Quitline will be eligible for inclusion in this proposed study if they (1) are 25 years of age or younger, (2) report having taken drugs within the past 30 days, (3) are able to communicate in Chinese, (4) agree to receive counselling via a messaging app (such as WhatsApp or WeChat), and (5) verbally consent to join the follow-up intervention. We will exclude potential subjects who have communication barriers and those who are undergoing other drug-misuse recovery treatments.

Because no previous study has conducted a brief telephone-based MI intervention, the sample size for the proposed RCT has been calculated according to a previous RCT that involved a computer-based MI intervention [18]. In this previous RCT, the mean number of drug-misuse consumptions per day decreased from 11.94 at baseline to 5.52 at 12 months for participants in the intervention group, and 9.22 at baseline to 8.61 at 12 months for those in the control group. The effect size was 0.64 for the MI intervention on drug-misuse reduction, with reference to the control group [18]. Based on these results, to detect a two-sided significant difference between groups with a power of 80 % and a significance level of 5 %, which are commonly accepted metrics for behavioural studies, the required sample size for this proposed RCT has been estimated to be 40 participants in each group. Given an expected retention rate of approximately 60 % at the 12-month follow-up, the target number of participants will be at least 134 (67 per group).

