### Data analysis

Data analysis will be performed using the Statistics Package for the Social Sciences (SPSS) version 25.0 for Windows (SPSS Inc., Chicago, IL, USA). Analyses will be conducted on an intention-to-treat basis, with missing-value substitutions based on the last observation carried forward. A two-sided statistical significance level of 0.05 will be adopted for all analyses.

Descriptive statistics will be used to detail participants’ demographic characteristics and drug misuse profiles. Frequencies and percentages or means and standard deviations will be used to present categorical data and continuous data, respectively. The differences between intervention and control groups, in terms of sociodemographic factors and outcomes, will be compared using a chi-square test for categorical variables and by an analysis of variance for continuous variables.

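### The 80% power is worked out for about 40 observed 12-month outcomes per group, but the planned analysis carries the last observation forward in all 67, and its power is not stated

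*Protocol article*

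**What the plan says.** The section on participants and sampling (Protocol article) takes its planning figures from an earlier trial of a computer-based intervention. In one arm of that trial, mean consumption "decreased from 11.94 at baseline to 5.52 at 12 months for participants in the intervention group". The comparison arm moved much less: "9.22 at baseline to 8.61 at 12 months for those in the control group". The article reports that "The effect size was 0.64 for the MI intervention on drug-misuse reduction, with reference to the control group". The design aim, in per cent, is "to detect a two-sided significant difference between groups with a power of 80 % and a significance level of 5". On that basis, the article says, "the required sample size for this proposed RCT has been estimated to be 40 participants in each group". The allowance for loss rests on this premise: "Given an expected retention rate of approximately 60 % at the 12-month follow-up". From it the article concludes that "the target number of participants will be at least 134 (67 per group").

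The Data analysis section sets an intention-to-treat analysis "with missing-value substitutions based on the last observation carried forward". Multiple imputation under missing at random appears only under Exploratory analysis, as a sensitivity analysis. The Outcomes section defines the primary outcome as a change from baseline to 12 months. The Measures section and Table 1 collect self-reported drug misuse at baseline, 1 week, and 1, 3, 6, 9 and 12 months. The intervention lasts 6 months.

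**The concern.** Dividing 40 by 0.6 is the right inflation if those lost are left out and the 40 who remain show the full effect. The analysis section describes something else: all 67 per group are analysed, and about 27 of them contribute an earlier value in place of the 12-month one. Someone lost in the first weeks contributes a value close to baseline, which pulls the groups together. Someone lost after month 6 contributes an end-of-treatment value as though it were the 12-month result. The sample-size section makes no allowance for either.

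With two-fifths of the primary outcome expected to be filled in this way, the power of the trial turns on the content of those values. A reader who takes the 80% at face value is relying on a figure that was not derived for the analysis that will be run.

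**Working it through.** **Inputs from the article.** Effect 0.64; two-sided 5%; 80% power; 40 per group with data; 60% retention; 67 per group randomised; means 11.94 to 5.52 (intervention) and 9.22 to 8.61 (control).

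**1. Reproduce the plan's figures.** A two-sample t-test at 0.64, 80% power and two-sided 5% needs 39.3 per group, so 40; power at 40 is 80.7%. Inflation: 40/0.6 = 66.7, so 67, or 134 in total. Both stated numbers hold.

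**2. Put the effect on the change scale.** The mean reductions are 11.94 − 5.52 = 6.42 and 9.22 − 8.61 = 0.61, a difference of 5.81. If 0.64 is that difference divided by the SD of change (an assumption; the article does not give the SD), the SD is 5.81/0.64 = 9.08. In SD units the completers' mean changes are 6.42/9.08 = 0.707 and 0.61/9.08 = 0.067.

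**3. Model the analysis of all 67.** Two quantities must be assumed, because the article states neither:
- f, the share of the 12-month effect held in dropouts' carried-forward values;
- s, the SD of dropouts' change as a fraction of the completers' SD.

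With 60% completers and 40% dropouts in each group:
- difference = 0.64 × (0.6 + 0.4f);
- variance within a group = 0.6 + 0.4s² + 0.24 × [(1 − f) × mean]², averaged over the two groups;
- d = difference / √variance, with power from the t-test at 67 per group.

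**4. Worked case: every dropout carries baseline forward exactly (f = 0, s = 0).** Difference = 0.6 × 0.64 = 0.384. Variances: 0.6 + 0.24 × 0.707² = 0.720 and 0.6 + 0.24 × 0.067² = 0.601; average 0.661. d = 0.384/√0.661 = 0.384/0.813 = 0.472. Power 77.5%.

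**5. Other cases.**

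| Share of effect in carried values (f) | s = 0 | s = 0.5 | s = 1 |
|---|---|---|---|
| 0 | 77% | 72% | 57% |
| 0.25 | 90% | 85% | 72% |
| 0.5 | 96% | 94% | 83% |
| 1 | over 99% | 99% | 96% |

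If the overall SD is simply left unchanged, f = 0 gives d = 0.384 and power 60%. Hence about 57-60% for dropouts with no effect and the completers' spread.

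**6. Break-even for 80%.** f is about 5% when s = 0, about 15% when s = 0.5, and about 40% when s = 1.

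**7. Where 0.64 came from.** The article does not say whether it was estimated in completers or by intention to treat. If it was already an intention-to-treat estimate, diluting it again counts the loss twice. Power at 67 per group with d = 0.64 is then about 96%.

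**The case against.** The strongest reply is that nothing is miscalculated and that dividing by expected retention is routine. That is correct, and the point is not an arithmetic error.

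A reader might go further than the mismatch and infer that the trial's power is only 60-77%. The documents do not support that, for four reasons.
- It requires every lost participant to carry baseline forward, so all of them would have to be lost before the 1-week call. There are five follow-ups before month 12, and a participant who misses one call is contacted again at the next.
- The 60% end needs dropouts with no effect yet a full spread of change, or the use of 0.64 for the 12-month level. The primary outcome is change, and exactly zero change cannot have the completers' SD. The level difference in the earlier trial is 8.61 − 5.52 = 3.09, not 5.81, so 0.64 is not shown to be a level effect.
- For change under literal baseline carry-forward the shortfall is only two to three points, and it disappears once carried values hold about 5% of the effect.
- Constant loss over 12 months (an illustrative assumption) would give a mean carried effect of about 39% if the effect grows linearly to month 12, or about 66% if it is complete by month 6. Most spreads would then put power above 80%.

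It is also fair that the planned adjusted generalised estimating equation model could shift all these figures, and that the article condenses a fuller protocol. What stands after all this is that the article states both the basis of the 80% and the rule for missing values, and that they describe different analyses.

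**Conclusion.** The point holds as a mismatch, not as a demonstrated loss of power. The figures of 40 and 67 are right. The 80% belongs to about 40 participants per group with observed 12-month data, and the planned analysis is of 67 per group with about 40% of values carried forward. The power of that analysis runs from about 57% to 96% or more, depending on the effect and spread in the carried-forward values and on how 0.64 was estimated. The reference case for the primary outcome, exact baseline carry-forward, gives about 77%. These figures rest on a comparison of mean change between two groups, equal 40% loss in both, and an SD of change of 9.08 inferred from the article's own means and effect size.

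Power above 80% would not settle the matter either. Where it comes from values frozen around the end of treatment, it is power to detect an early effect labelled as a 12-month one. The point merits correction, but it does not undermine the enrolment target.

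**What to change.** Make the multiple imputation already planned as a sensitivity analysis the primary handling of missing outcomes, or use a likelihood-based repeated-measures model that draws on the scheduled follow-ups. Move last observation carried forward to a sensitivity analysis. In the sample-size paragraph, state that the 80% refers to about 40 observed 12-month outcomes per group at an effect of 0.64, and say whether that effect came from completers or from an intention-to-treat analysis.

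If last observation carried forward stays primary, give its power as a range with the assumed effect and spread among dropouts set out beside it. Neither 80% nor 60-77% should stand alone.

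The cost is a revised sample-size paragraph, a revised missing-data sentence, slightly more analysis work and a more qualified power statement. No new data and no change in enrolment are needed.
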